**Fig. 2 Fig2:**
[figure not shown]
iCPR risk calculator example. © 2017 Epic Systems Corporation. Used with permission

#### Smart sets

The content of the smart sets needed to vary by the level of patient risk (low, intermediate, or high). To provide this functionality, we chose to leverage EPIC functionality which allowed suppressing components of the smart set based on patient factors (weight and age) as well as risk score. We developed one smart set for sore throat and one for cough. The smart sets included documentation for progress notes, laboratory orders, prescription orders, diagnoses, patient instructions, and level of service (Fig. 3).

**Fig. 3 Fig3:**
[figure not shown]
iCPR smart set example. © 2017 Epic Systems Corporation. Used with permission

### Usability testing

#### “Think aloud”

Think aloud testing was performed to determine the usability of the individual iCPR components. Primary care providers, six from the University of Utah and four from the University of Wisconsin, were selected from volunteers to form a convenience sample. Inclusion criteria required that participants worked in Family Medicine, Internal Medicine, or Urgent Care clinics, spent at least 50% of their time providing clinical care, and were currently using the EHR system in which the CDS would be imbedded. Each participant was presented with a written clinical case describing a patient with low, intermediate, or high risk of either strep pharyngitis or pneumonia. Under scripted instruction from the interviewer, the participant was directed to perform different aspects of clinical documentation including opening the chart, entering patient data, creating a progress note, and placing appropriate orders. While interacting with the tool, participants were strongly encouraged to think out loud and to verbalize their thought process. After interacting with the tool, the participant was asked a few specific questions about general attitudes toward the tool. Each session lasted 25–45 min. Screen capture and audio were recorded and put into categories by two independent coders.

#### “Near live”

The goal of the near live testing was to determine how the tool fits with providers’ workflows. Eight primary care providers from the University of Wisconsin were selected from volunteers. Inclusion criteria were similar to those used in the think aloud testing. In a clinic office setting, each participant interacted with a simulated patient, an actor who was trained to portray a case of low-, intermediate-, or high-risk strep pharyngitis or pneumonia. The participant interacted with the patient actor while navigating through the CDS tool. Participants were told to think out loud if they had any challenges or positive experiences with the tool. The study staff observed the sessions to answer questions, troubleshoot the software, and provide the physical exam information. After completing the testing, participants were asked about their reaction to specific components of the tool and for suggestions for improvement. Every participant completed at least one case, and two completed two cases each. The duration of each session was between 25–45 min. Two independent coders reviewed all recorded screen captures and the transcribed audio. Verbalized thoughts and participant actions were coded. Based on usability testing, multiple modifications were made to the wording and format of the alerts, calculators, and smart sets. Also, specific ranges of risk were included in the calculator and some non-antibiotic medication orders were removed from the smart sets.

### Outcomes

#### Evaluation framework

RE-AIM is a five-part framework designed to enhance the quality, speed, and public health impact of efforts to translate research into practice [20]. The five dimensions of RE-AIM are reach, effectiveness or efficacy, adoption, implementation, and maintenance. The framework has guided successful implementation and dissemination projects across disease entities and health care settings [21–23]. It encourages a study that balances concern for internal and external validity, giving equal attention to efficacy and to generalizability and dissemination potential [24]. Our evaluation plan will incorporate all five dimensions of the RE-AIM framework. REACH: To ensure that we reach the targeted audience, we will evaluate the percent of primary care clinics at each institution that participate in the study and compare the specialty, size, and location of participating versus non-participating clinics. EFFICACY: To determine efficacy of the ICPR tool, we will evaluate the clinical practice outcomes discussed below. ADOPTION: To evaluate adoption of the iCPR tool, we will determine provider utilization by clinic and institution as discussed in the process outcomes section below. IMPLEMENTATION: Fidelity of iCPR tool delivery will be evaluated via the number of attendees at academic detailing sessions and use of all components of the tool. MAINTENANCE: Comparison of adoption and efficacy trends from year one to year two will be used to determine whether the tool has become routine practice at the two institutions.

#### Clinical data collection

All clinical data will be collected via the EHR. Provider data will include level of training (physician, resident physician, NP, PA), gender, and date of birth. Provider data is stored in the provider profile within the EHR. Patient data will be collected for patients that have iCPR eligible encounters during the study period. Patient data will include date of birth, allergies, comorbidities, and any other encounters within 1 week of the qualifying encounter. Encounter data will include clinic site, date of visit, medication orders (including antibiotics), test orders (rapid strep test, throat culture, and chest x-ray), test results, diagnoses, trigger for iCPR (reason for visit or diagnosis), use of iCPR components, and score on iCPR calculator. Collection of data in the control group will use a “shadow” simulation to determine which encounters meet criteria for iCPR trigger even though the tool does not actually trigger. The final data set will be shared with the principal investigator, co-investigators, and the data-coordinating site at Boston University. The funding agency NIAID will also have access to use the data set.

#### Clinical practice outcomes

The study outcomes were designed to evaluate changes in clinical practice related to iCPR tool use. The primary outcome is the difference in antibiotic prescribing rates in iCPR patient encounters in intervention versus control providers. Secondary outcomes include the rates of rapid strep, throat culture, and chest x-ray ordering and the class of antibiotics prescribed. To measure the safety of clinical care, we will evaluate rates of additional encounters to primary care or urgent care, hospitalization, and prescription of respiratory tract antibiotics within 1 week of the index encounter.

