#### Comparing workflows

The current iCPR tool is adapted from the previous iCPR tool but tailored to fit the current sites’ unique workflows. The iCPR tool design was developed by an interdisciplinary team of experts in primary care, usability, and clinical informatics. Interviews were held with providers, clinic managers, and medical assistants at each site to determine general clinic workflows as well as specific workflows for rapid strep and chest x-ray testing.

These interviews demonstrated that workflows varied dramatically by institution with some variation by clinic and even by provider within a clinic. For example, a major difference between institutions was that University of Utah providers heavily leveraged an EHR-assisted documentation pathway called “NoteWriter.” This structured documentation template has the ability to create pick-list histories based on the patient’s chief complaint. In this workflow, medical assistants record a structured history that the provider then reviews and confirms with the patient. The structured history, as well as the vital signs and, if used, structured physical exam then populates the iCPR tool. This decreases the need for duplicate documentation. Another workflow difference was a variable approach among clinics to rapid strep testing including which clinic personnel review test results and whether patients remain in the clinic until results are complete.

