### Tool design considerations

The team also reviewed all of the iCPR tool features and designs to ensure it met the needs of the diverse clinics. This included examining the (1) tool activation level, (2) timing of alerts, (3) integration into clinical workflow, (4) alert triggers, and (5) interruptive versus non-interruptive alerts.Tool activation: We chose to activate the tool based on the clinic where the encounter was performed instead of at the provider level. The clinic was chosen to coincide with the unit of randomization and to prevent study contamination from providers that worked at multiple clinics.Timing of alerts: It was clear from interviews with providers that there was variation in when they ordered tests and antibiotics during the patient encounter. We chose to base the main trigger on the reason for visit despite infrequent completion of this field by providers in the original iCPR clinical site [9]. Relying on reason for visit as the main trigger made iCPR available early in the encounter and throughout the subsequent workflow. We also included a secondary trigger, similar to the original iCPR design, that would occur toward the end of the encounter based on diagnosis and a combination of diagnosis and orders. While the secondary trigger may not be frequently used, it might allow providers to change decisions or at least alert them to considerations for future encounters. We also automatically triggered alerts in the provider’s inbox and when the provider reopened an encounter after a relevent test had resulted.Integration into clinical workflow: The iCPR needed to be integrated into active clinical practice without disrupting patient care. It is clear that without integration into workflow, CDS tools are not used [15]. This led to some individualization between institutions including the use of NoteWriter at some sites. We also decided to make iCPR as flexible as possible in order to facilitate the integration into various workflows. This included the ability for providers and nurses to use bundled ordersets based on test results and for support of telephone encounters or patient portal encounters.Alert triggers: Another guiding principle was limiting the number of inappropriate triggers. We balanced trigger sensitivity and specificity, erring on the side of specificity at the cost of missing some potentially appropriate encounters. Triggers were determined by reviewing clinic data from the previous year for the final encounter diagnoses based on available reasons for visit and whether antibiotics were prescribed. We found that only three reasons for visit commonly resulted in diagnoses that we wanted to affect. Based on these, we chose “cough/chest congestion,” “URI (upper respiratory infection),” and “sore throat” as the reason for visit triggers. For triggers based on diagnosis and antibiotics, we chose the narrowest diagnoses and only antibiotics commonly used in respiratory infections (Table 2).Interruptive vs non-interruptive alerts: Interruptive alerts interfere with workflow and force users to acknowledge the alert, potentially increasing clinician frustration and alert fatigue [16, 17]. Given the broad nature of the three reasons for visit triggers we chose, we knew that iCPR was likely to trigger at times when it would not be helpful, such as when a patient with asthma or sinusitis presented with a cough. Based on the risk of inappropriate triggers as well as provider opinions from the interviews, we chose to use non-interruptive alerts for the reason for visit triggers. We explored options for non-interruptive alerts for the diagnosis triggers, but there were no mechanisms within the EHR that allowed us to do this. Thus, we opted for interruptive alerts if iCPR was triggered by a diagnosis or diagnosis plus antibiotic prescription.

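### The primary outcome counts antibiotics at the iCPR encounter, so a prescription moved to a later contact after a test result can look like a reduction

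*Protocol article*

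**What the plan says.** All references are to the protocol article.

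- **Clinical practice outcomes** defines the primary outcome: "The primary outcome is the difference in antibiotic prescribing rates in iCPR patient encounters in intervention versus control providers". The same section lists "prescription of respiratory tract antibiotics within 1 week of the index encounter" among the safety measures, with additional primary or urgent care encounters and hospitalization.
- **Patient inclusion and exclusion criteria** builds the analysis set from visits with a provider at a study clinic that meet the trigger criteria.
- **Tool design considerations** says the tool's flexibility included "the ability for providers and nurses to use bundled ordersets based on test results and for support of telephone encounters or patient portal encounters". Alerts also fire in the provider's inbox and "when the provider reopened an encounter after a relevent test had resulted".
- **Intervention and control groups** says control clinics had no access to the tools.
- **Comparing workflows** reports that clinics' approaches to rapid strep testing varied, including "which clinic personnel review test results and whether patients remain in the clinic until results are complete".
- **Clinical data collection** already extracts "any other encounters within 1 week of the qualifying encounter".
- **Power calculation** assumes a control prescribing rate of 30-40% and an absolute decrease of 10 points.

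**The concern.** The intervention can change whether an antibiotic is given, and also when and through which channel it is ordered. An outcome counted at the visit cannot separate the two. If a patient is tested, goes home, and is prescribed for by telephone, through the portal or by a nurse, the visit may be scored as having no antibiotic. The later order then appears among the safety events. The same prescription would be a success on one outcome and an adverse signal on another.

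The stated aim is the tool's effect on antibiotic prescribing, and the background rests on antibiotic overuse. What matters for that aim is whether the illness was treated with an antibiotic. If deferral is more common where the tool is active, the primary difference overstates the fall in antibiotic use. More encounters would not correct that.

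**Working it through.** **What there is to reproduce.** The article gives no deferral share and no proportion of encounters in which the decision waits for a test. No plan figure can be checked on this point, so only a range is possible.

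**Inputs**
- Prescribing rate p: 0.30 to 0.40 (Power calculation), assumed to apply to test-dependent encounters as well.
- Share of encounters with a test-dependent decision, t: 0.10 to 0.30 (assumption).
- Extra share of those prescriptions moved to a later, uncounted contact in the intervention arm, d: 0.10 to 0.20 (assumption).
- Planned effect: 10 points (Power calculation).

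**Formula.** With no true difference in antibiotic use, the apparent reduction is p × t × d.
- Low end: 0.30 × 0.10 × 0.10 = 0.003, or 0.3 points.
- High end: 0.40 × 0.30 × 0.20 = 0.024, or 2.4 points.

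**The same per 1,000 intervention encounters**
- High end: 400 prescriptions in all; 300 test-dependent encounters carry 120 of them; 20% of 120 is 24 moved. The visit-level count is 376, so 37.6% against 40.0%.
- Low end: 300 prescriptions in all; 100 test-dependent encounters carry 30; 10% of 30 is 3 moved. The count is 297, so 29.7% against 30.0%.

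Relative to the planned effect, this is 0.3/10 = 3% to 2.4/10 = 24%. If all the moved orders fall within a week, the one-week antibiotic safety rate rises by the same 0.3-2.4 points.

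**Cross-check on another scale.** Each 1% of all prescriptions deferred in excess of control shifts the primary difference by 0.3 to 0.4 points. An excess of 5% gives 1.5-2 points and 10% gives 3-4. For deferral alone to produce the whole planned effect, the excess would have to be 10/40 = 25% or 10/30 = 33% of all prescriptions.

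**Direction.** Only d, the excess over control, matters. Intervention-only functions for telephone, portal and nurse ordering could make d positive. The alert on a reopened encounter could pull the other way, by keeping in the original visit an order that a control clinic places elsewhere.

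**Return visits.** A return visit that triggers again is an iCPR encounter in its own right. An antibiotic ordered there is counted, but the illness then contributes one prescription over two encounters, not one over one. These prescriptions are diluted, not lost.

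**The case against.** The strongest reply is that deferral is already measured. One-week antibiotics and extra encounters are compared between arms, and the three-level model applies to the other clinical outcomes as well. A shift within a week would show up beside the primary result. An encounter-level outcome also fits the section's stated purpose of evaluating changes in clinical practice. That largely stands: a reader might infer that later antibiotics go unobserved, and they do not. What remains is that a separate safety rate neither corrects the primary estimate nor tells the reader how to combine the two.

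The article also does not say how orders placed after a result are attributed. Orders in a reopened encounter may already count, and the full protocol or analysis plan may settle this. That stands too, so the attribution rule is something to state or confirm, not an error shown.

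Third, bias needs deferral that differs by arm. Control clinics can also prescribe after a result. The variation in whether patients wait was found in interviews before deployment, and clinics were then randomized. A reader might infer a demonstrated bias in favour of the tool; the text describes a route that differs by arm, not a net effect.

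Finally, a reader might multiply the share of test-dependent encounters by the share deferred and get 1-6 points (0.10 × 0.10 to 0.30 × 0.20). That product is a percentage of prescriptions. As a shift in the encounter rate it must be multiplied by the 30-40% prescribing rate, which gives the smaller range above.

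**Conclusion.** The point holds in a limited form. The primary outcome is tied to the triggering visit, one-week antibiotics sit outside it as a safety measure, and the functions that support later ordering exist in one arm only. Reduction and deferral can therefore be confused in the primary comparison.

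Under the stated assumptions the apparent reduction is about 0.3-2.4 points against the planned 10. Two of the three inputs are assumed, so this range is an illustration. Deferral is unlikely to account for a full 10-point effect, but it could be a material part of a smaller one.

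The documents do not support the inference that the primary outcome is invalid or must be replaced. Nor does the point take a view on when an antibiotic should be given; it concerns only what is counted.

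**What to change.** 1. State, or confirm from the full protocol, that an antibiotic ordered in a reopened encounter or a linked telephone, portal or nurse contact is attributed to the index encounter, by the same rule in both arms.
2. Keep the encounter-level primary outcome. Replacing it in a trial already running since October 2015 is debatable and not needed.
3. Prespecify a key supporting analysis with the same three-level model: any respiratory-tract antibiotic at the index encounter or within 7 days. Use one observation per illness episode, defined as the first qualifying encounter with none in the preceding 7 days.
4. Claim reduced antibiotic use only if this analysis agrees with the primary. Define agreement in advance, preferably by the estimate and its interval.
5. Keep the one-week safety outcome in all analysed patients at the randomized clinics. Restricting it to those without an index prescription would condition on something the tool is meant to change, and the arms would no longer be comparable. Report later antibiotics that follow a positive test separately.

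**Cost.** Encounters within 1 week are already extracted, so the work is wording, a linkage rule and one further model. The supporting analysis will count a few unrelated later antibiotics in both arms, will use fewer observations because repeat encounters are collapsed, and may show a slightly smaller effect. The sample size basis of the primary outcome is unchanged.

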#### Process outcomes/iCPR implementation

Success of clinical decision support relies on uptake of the tools into practice. It is critical to determine how the tool is being used in practice in order to understand why clinical practice outcomes changed. The process measures will help determine iCPR use in general as well as the use of specific components of the tool. Process outcomes will include completion of the risk calculator and use of the individual components of the smart sets. We will use Normalization Process Theory (NPT) to better understand the factors that affected implementation in individual clinics. NPT provides a framework to evaluate organizational impact as well as facilitators and barriers to implementation [25]. The 16-item NPT questionnaire contains questions in four domains: sense-making, participation, action, and monitoring. Questionnaires will be completed by intervention clinic medical directors and managers at baseline and every 6 months until completion of the 2-year study. Changes over time will be evaluated and qualitative assessment will be done for differences between clinics with high and low adoption.

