#### Alerts

At the University of Wisconsin, a standard EPIC alert is used to inform providers when a patient is appropriate for iCPR. Providers are familiar with seeing these alerts for other conditions. The alert specifies why iCPR was triggered and includes a link to the risk calculator. In addition to this alert, the University of Utah placed an additional tab in NoteWriter. This tab, called “Provider Score,” was populated with the appropriate iCPR criteria (Centor, McIsaac, and/or Heckerling) based on the reason for visit. In all other cases, it was blank. The Provider Score tab of NoteWriter draws information from vital signs and structured history and physical exam documentation. It can also be completed ad hoc. After completion, the score and interpretation are visible to the provider. The calculator score also drops directly into the clinical note.

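### Risk-calculator completion may not mean the same thing at Utah and Wisconsin, so a pooled contrast of high- and low-adoption clinics can partly reflect the software build

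*Protocol article*

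**What the plan says.** Under Process outcomes/iCPR implementation, the protocol article states: "Process outcomes will include completion of the risk calculator and use of the individual components of the smart sets". The Evaluation framework section rests the adoption dimension on these outcomes: "we will determine provider utilization by clinic and institution as discussed in the process outcomes section below". Questionnaires go to medical directors and managers of intervention clinics, and "qualitative assessment will be done for differences between clinics with high and low adoption". Data monitoring tracks triggering, calculator completion and smart set use weekly by clinic.

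The tool is built differently at the two institutions:

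- **Utah.** Comparing workflows says that "medical assistants record a structured history that the provider then reviews and confirms with the patient", and continues: "The structured history, as well as the vital signs and, if used, structured physical exam then populates the iCPR tool". The Alerts section describes an extra tab: "The Provider Score tab of NoteWriter draws information from vital signs and structured history and physical exam documentation". It adds: "It can also be completed ad hoc". The score then goes into the clinical note. Utah also has the standard alert.
- **Wisconsin.** The Alerts section says: "At the University of Wisconsin, a standard EPIC alert is used to inform providers when a patient is appropriate for iCPR". The alert carries a link to the calculator. No NoteWriter tab is described.
- **Both.** Risk calculators describes flow sheets with yes/no buttons. Age (McIsaac) and heart rate and temperature (Heckerling) are filled automatically, and the sites are not distinguished.

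Statistical analysis models component use with random effects for practice and provider and with fixed effects for provider training and gender. The clinical-outcome model, by contrast, includes the randomization strata, which contain institution.

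**The concern.** An adoption measure compared across clinics should take about the same provider effort in each of them. Here, part of a Utah score can come from documentation that would be done anyway, whereas a Wisconsin score needs the provider to open the flow sheet and answer most items. The Discussion acknowledges that design and workflow vary between the two systems, but nothing in the adoption assessment takes this up.

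What is at stake is the explanation of the result, not the result itself. The article wants the process measures in order to understand why practice changed, and it plans a subgroup analysis by institution. If completion is higher at Utah partly because of pre-filling, it could be read as stronger uptake there. If clinics are sorted into high and low adoption over both institutions together, differences in questionnaire responses could be credited to adoption when they follow the institution. The training and gender comparison could also pick up the build difference if the provider mix differs between institutions.

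**Working it through.** The plan gives no figure for this point, so there is none to reproduce. The check has two parts.

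**1. How many items can be filled without the provider answering them in the calculator?** The items are in Table 3 and the automatic fields in Risk calculators, Alerts and Comparing workflows. Assumptions: the Utah structured history holds lack of cough, history of fever and asthma, and age carries over to the Utah tab. The Utah counts are therefore upper limits.

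| Rule | Items | Flow sheet, automatic | Utah tab, no structured exam | Utah tab, structured exam used |
|---|---|---|---|---|
| Centor | 4 | 0 | 2 (history) | 2 + 2 exam = 4 |
| McIsaac | 5 | 1 (age) | 1 + 2 history = 3 | 3 + 2 exam = 5 |
| Heckerling | 5 | 2 (heart rate, temperature) | 2 + 1 history = 3 | 3 + 2 exam = 5 |

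The difference is one of degree. It lies in the history and exam items, and a full score from documentation alone needs the structured exam.

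**2. What could this do to the adoption figures?** This part is illustration. Only the clinic counts come from the article.

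- From Table 1: 12 intervention clinics at Wisconsin and 6 at Utah, so 6/18 = 33% are at Utah.
- Assumed: deliberate use *u* is the same at both institutions, and a share *a* of otherwise unused Utah encounters is counted as complete through pre-filling.
- Counted completion at Utah = *u* + (1 − *u*) × *a*; at Wisconsin it is *u*.

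For *u* = 0.30:

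- *a* = 0.10: 0.30 + 0.70 × 0.10 = 0.37
- *a* = 0.25: 0.30 + 0.70 × 0.25 = 0.475
- *a* = 0.50: 0.30 + 0.70 × 0.50 = 0.65

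To see the effect on a high/low split, true use per clinic was drawn from a beta distribution with mean *u* and an assumed between-clinic SD of 0.08. The 18 clinics were ranked on counted completion and the top 9 called high adoption (20,000 runs). Without any artefact the expected number of Utah clinics in the top half is 6 × 9/18 = 3. Each cell gives counted Utah completion, then the mean number of the 6 Utah clinics in the top 9.

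| *u* | *a* = 0 | *a* = 0.10 | *a* = 0.25 | *a* = 0.50 |
|---|---|---|---|---|
| 10% | 10%; 2.99 | 19%; 5.21 | 32.5%; 6.0 | 55%; 6.0 |
| 30% | 30%; 3.01 | 37%; 4.45 | 47.5%; 5.91 | 65%; 6.0 |
| 50% | 50%; 3.01 | 55%; 4.03 | 62.5%; 5.47 | 75%; 6.0 |

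Under these assumptions, a pre-fill share of one quarter puts nearly all Utah clinics in the high group although true use is equal. The split into halves is a device of this check; the article states no cut-point.

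**The case against.** The strongest reply is that the article never says a pre-filled Utah score counts as completion without an act by the provider. The counting rule may stand in a document not shown. The remark on ad hoc entry only adds a manual route, the provider confirms the history, and exam items fill only if the structured exam is used. Some items fill automatically in the flow sheets too, and Utah providers also have the alert link. Utilization by institution is reporting, with no stated test between institutions, and it keeps the two builds apart. Smart set use is already a process outcome, the high/low contrast is qualitative, and monitoring adds smart set counts and chart review.

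All of this stands, and it rules out several stronger readings that a reader might infer:

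- *That the institutional adoption figures cannot be interpreted.* The article does not show that pre-filled scores are counted, and smart set use remains available.
- *That all 6 Utah intervention clinics, a third of the total, record scores automatically.* Tool design considerations places NoteWriter at some sites, and the exam feed is conditional.
- *That a gap of a particular size is to be expected.* Any such figure comes from assumed inputs.
- *That monitoring would miss non-use.* High completion with little smart set use would be visible in the weekly reports.

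The reply does not remove the narrower point. Even if every counted completion needs a provider action, that action takes less work where history and exam items are already filled. The article contrasts high- and low-adoption clinics without saying that this is done within institution, and it names no institution term in the component-use model.

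**Conclusion.** The point holds in limited form. Calculator completion may not be equivalent at the two institutions, so the reading of completion by institution and a pooled contrast of high- and low-adoption clinics can partly reflect the Utah and Wisconsin builds.

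The size of any artefact is unknown. It depends on whether and how pre-filled scores are counted, on how often the structured exam is used, and on how NoteWriter use varies between clinics; the article gives none of these. The illustration shows only that a moderate effect would be enough to turn a pooled split largely into a split by institution.

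Only process and adoption results are touched. The primary comparison of antibiotic prescribing is randomized within institution strata and does not use calculator completion.

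**What to change.** 1. Classify clinics as high or low adoption within institution.
2. Use smart set use, which is already collected and is not described as pre-filled, as the adoption measure for statements across institutions.
3. State what counts as a completed calculator in each build. Report completion separately by institution and, where the EHR records it, by entry route (NoteWriter tab or flow sheet). Do not restrict completion to calculators opened through the alert link: the Utah tab is a designed part of the tool there, and its genuine use should count.
4. Add institution as a fixed effect to the component-use model under Statistical analysis.

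No change to trial conduct is needed. The cost is slightly more analysis, fewer clinics in each within-institution contrast (12 and 6), and possibly a lower headline adoption figure at Utah. The article does not show whether entry route is recorded, so that part of item 3 depends on the EHR; the other items do not.
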